**4.** **Location of signed consent forms and data collection**

Signed consent forms and case report forms will be stored in a locked file at the STVHCS and MARC clinic locations approved research sites. Access to these rooms is limited to designated research personnel.

**4. Human Subjects**

**4.1 Compensation and Costs**

Participants will be compensated $25.00 per visit for a total of $100.00 for participating in the study. Study drug will be provided to subjects at no cost. There will be no cost to collect or process research specific biomarkers. Patient’s health insurance company will be responsible for the costs of treatments and procedures that would be done whether or not they take part in this study, such as, digital rectal exams, and transrectal ultrasound (TRUS) with prostate biopsy.

**4.2 Risks to subject**

There is a small chance that the subject could experience bleeding or infection from the prostate biopsy. Under the proposed protocol, each study site will use their standard procedures for obtaining the prostate biopsy tissue that will consist of a minimum of 12 cores. Prophylactic antibiotics will be prescribed per site’s standard of care. There would be no psychological, legal or social risks associated with the study. Side effects with finasteride include both advantages and disadvantages. Advantages from finasteride include improved urinary stream, reduced urinary frequency and nocturia, and increased hair growth if male pattern baldness is present. Disadvantages include decreased ejaculate volume, libido, and erectile dysfunction and gynecomastia. These adverse experiences generally did not lead to discontinuation of the study drug. Finally, there is potential risk that a delay in diagnosis of prostate cancer by as much as 3 months could affect the outcome of treatment. Evidence would suggest that this risk is low, especially due to the risk range selected for study and the fact that most prostate cancers develop over a period of years to decades.

[Information from the U.S. Food and Drug Administration (FDA) Drug Safety Communication on June 9, 2011 resulted in the following text added to the informed consent form] - Finasteride was studied in a clinical trial of almost 19,000 men, sponsored by the National Cancer Institute. The study was designed to determine if the drug could prevent the development of prostate cancer. The final results of the study showed that finasteride, taken over 7 years, reduced a man’s risk of prostate cancer by about 25%. It also found an increase in detection of a less-common, more aggressive type of prostate cancer. While it is possible that this medication may cause this more aggressive tumor, it was also found that in men who were taking finasteride, detection tests (PSA and prostate rectal examination) and prostate biopsy more easily detected the aggressive tumors which were more commonly missed in men who were not taking the medication. It is this improved detection of prostate cancer that it is hoped will be seen in this 3-month period.

**4.3 Special precautions: Procedures for** **Minimizing Risks, Treating Adverse Effects to Ensure Subject Safety**

Risks of phlebotomy: risks will be minimized by using universal precautions and standard clinical procedures for phlebotomy. Blood draws will be performed by appropriately trained personnel who pay careful attention to technique and abide by established standards (use of sterile needles, blood and body fluid precautions); ensure that tubes are within their expiration date; and study protocol procedures are followed.

Prostate Tissue Collection: Risks are minimized by using visits in conjunction with Standard of Care. Biopsy procedures will be completed by study physician who is credentialed to perform this procedure. Appropriate protocol technique will be utilized with care taken to minimize risks. Privacy will be offered as per standard care. Subject data will be examined and subjects queried for adverse events. The data will be periodically reviewed by the Principal Investigator to ensure quality control and safety.

**4.4 Alternative Treatments**

Patients who are eligible for the proposed study will be receiving the current standard of care: prostate biopsy. In general, prostate biopsy would be offered at a next available time or depending on the patient’s schedule. On average, the time between initial consultation for biopsy and the biopsy itself may range from 4-6 weeks or longer. As such, the delay for prostate biopsy by study participation would be in the range of 6-8 weeks.

**4.5 Confidentiality**

Protected Health Information may be shared with the researchers at The University of Texas Health Science Center at San Antonio (UTHSCSA). The Institutional Review Board (IRB) and Compliance Office of the University of Texas Health Science Center at San Antonio, representatives of the University Hospital System, Research Office,and South Texas Veterans Health Care System (STVHCS) Hospital, Audie L. Murphy Division, Research & Development and Compliance Offices. In addition, representatives of other groups that have the responsibility of monitoring and overseeing research studies, and the Food and Drug Administration (FDA). Maintaining confidentiality of patient-specific information will be top priority throughout all phases of the study. Patient data (PHI) will be compiled in a database and de-identified upon completion of analysis. Cases in the database will be identified by initials, patient identification number, the year of patient’s birth, and the date of biopsy. The database will not include information which can be identifiable with the link (or key). All electronic data will be stored in a password protected database in accordance with UTHSCSA computer-security policies. The identification number is actually a research record number that cannot be linked to the subject except by a key. This key will be maintained by the research staff in the enrollment log stored on a password protected UT Server. Informatics Data Exchange and Acquisition System (IDEAS) designed and maintained by the Department of Epidemiology and Biostatistics (DEB) will be used to manage data and monitor data entry. Identification of any specimens will be by patient study number assigned at time of trial entry. Parts of collected PHI may be photocopied and sent to a central location or may be transmitted electronically, such as by e-mail or fax.

**5. Safety Monitoring**

**5.1** **Adverse Events**

An adverse event (AE) is the appearance of (or worsening of any pre-existing) undesirable sign(s), symptom(s), or medical condition(s) occurring after a participant signs the informed consent even if the event is not considered to be related to the study. An AE can therefore be any unfavorable and unintended sign (including abnormal laboratory finding), symptom, or disease temporally associated with any study-related procedure or the use of study medication, whether or not considered related to the study-related procedure or the use of study medication.. This definition includes inter-current illnesses or injuries, and exacerbation of pre-existing conditions. Indicators of disease progression will not be reported as AEs. Any abnormal clinical test results (PSA, BMP and urinalysis) or other safety assessments (radiological scans or vital signs) that are associated with the underlying disease, unless judged by the investigator to be more severe than expected for the subject’s condition, are not to be reported as AE’s.

Adverse events that are directly related to research specific procedures (phlebotomy and prostate biopsy) will be graded for severity according to the NCI Common Terminology Criteria for Adverse Events (CTCAE), version 3.0 (available online at <http://ctep.cancer.gov/reporting/ctc.html>). If CTCAE grading does not exist for an AE, the grading descriptor of mild, moderate, severe, life-threatening, and death, or grades 1-5, will be used.

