**5.3 Collecting** **and Recording Adverse Events**

Any AE or SAE occurring during the study must be documented in the subject’s medical record in accordance with the investigator’s normal clinical practice and on the AE or SAE case report form (CRF) for the study. An adverse event that occurs after study consent is signed but before research-related procedures will be recorded as medical history.

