**5.4 Assessment of Causality**

The investigator is obligated to assess the relationship between any study-related procedure or study medication and the occurrence of each AE/SAE. The investigator will use clinical judgment to determine the relationship. Alternative causes, such as natural history of the underlying diseases, concomitant therapy, other risk factors, and the temporal relationship of the event to any study-related procedure or study medication will be considered and investigated.

Even in situations when an SAE has occurred and the investigator has incomplete information to include in the initial SAE report, the investigator will make an assessment of causality for every event prior to reporting it. The investigator may change his opinion of causality in light of follow-up information and amend the SAE case report form and report accordingly.

Adverse events will be reported annually to the IRB. SAEs meeting the IRB definition of Unanticipated Problems Involving Risk to Subjects or Others (UPIRSO) will be reported to the IRB within 7 days and within 48 hours if life-threatening or fatal. As Merck & Co will be providing finasteride and placebo, SAEs will also be reported to Merck within the same period. In addition, copies of all serious adverse experiences, which are possibly, probably, or definitely related to use of a Merck Product should be sent to Merck (Attn: Worldwide Product Safety; [contact]) within two working days. Additionally, any report of pregnancy occurring in association with use of a Merck Product should be sent to Merck (Attn: Worldwide Product Safety; [contact]).

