As noted below in our statistical section, the statistical power of this study will rely on having a minimum of 144 events (prostate cancer cases) in finasteride arm to evaluate the 3-month finasteride ‘challenge’ test as an adjunct to prostate cancer detection. We expect a positive biopsy rate of 40% in men with intermediate risk of prostate cancer but will increase accrual as needed to reach this minimum number of events. We anticipate that some men may ‘drop out’ of the study’s participation due to perceived problems with the medication (e.g., perceived sexual dysfunction[56]) or if they simply change their mind related to the prostate biopsy. We plan on regular follow-up with all participants to keep them abreast of the study’s progress as well as new developments in prostate cancer detection. We have found that these regular follow-up telephone calls help maintaining subject interest in the trial. We have made conservative expectations on subject recruitment from our large Urology practice for accrual and do not anticipate problems reaching this number of events within the time of the study.

**6.2. Specific Aim 2**: To evaluate serum PSA velocity after a 3-month finasteride 'challenge' as a biomarker for prostate cancer on biopsy.

*Rationale: This aim is first needed to confirm that under finasteride, PSA indeed dropped more for non-cases than for subsequent cancer* cases (PSA velocity differed between cases and non-cases) *and that on its own has good (comparable to PSA alone) operating characteristics (sensitivity, specificity, and AUC).*

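### The severity-grading rule names only phlebotomy and biopsy events, so the protocol does not require a grade for non-serious adverse events of the randomised drug

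*Protocol*

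**What the plan says.** Section 5.1 defines an adverse event broadly. It includes any unfavourable sign, symptom or disease "temporally associated with any study-related procedure or the use of study medication", whether or not it is judged related.

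The next paragraph of 5.1 sets the severity rule: "Adverse events that are directly related to research specific procedures (phlebotomy and prostate biopsy) will be graded for severity" under CTCAE version 3.0. A fallback follows: "If CTCAE grading does not exist for an AE, the grading descriptor of mild, moderate, severe", life-threatening and death, or grades 1 to 5, will be used.

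The other safety rules are wider than the severity rule:

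- Section 5.3: "Any AE or SAE occurring during the study must be documented" in the medical record and on the case report form.
- Section 5.4: the investigator must "assess the relationship between any study-related procedure or study medication and the occurrence of each AE/SAE".

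The protocol expects the drug to cause effects. Section 4.2 says: "Disadvantages include decreased ejaculate volume, libido, and erectile dysfunction and gynecomastia". The pitfalls paragraph in Section 6.1 anticipates that some men will leave "due to perceived problems with the medication".

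**The concern.** The randomised intervention is finasteride against a matching blinded placebo. Definition, recording and causality all cover it, but the one sentence that says which events receive a severity grade names two procedures and omits it. Men in both arms undergo both procedures, so the rule as worded leaves out the one exposure that differs by randomisation.

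At stake is the description of tolerability. The effects listed in Section 4.2 would usually not meet the seriousness criteria in Section 5.2, so for these events a severity grade is the ordinary way to separate a trivial complaint from a troublesome one. The protocol links drug tolerability to drop-out, and Section 1 foresees the challenge being considered for a very large number of men. A grade that sites were never asked to record cannot be supplied later by an analysis plan, so this is a collection rule drawn too narrowly and not a detail left for the plan.

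**Working it through.** No arithmetic applies: the point depends on no power, error rate or sample size, and the plan gives no figure to reproduce. The check sets the scope of each safety rule side by side and then follows one type of event through them.

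**Step 1. Scope of each rule**

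| Rule | Section | Study procedures | Study medication |
|---|---|---|---|
| Definition of an adverse event | 5.1 | covered | covered |
| Seriousness | 5.2 | covered (any event) | covered (any event) |
| Recording | 5.3; Table I at months 1, 2 and 3 | covered | covered |
| Causality | 5.4 | covered | covered |
| Severity grade | 5.1 | phlebotomy and biopsy | not named |

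Sections 3 (procedures and study calendar), 4.2, 4.3 and 6.1 contain no other severity rule.

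**Step 2. Does the fallback sentence widen the rule?** It speaks of an adverse event in general terms, but its condition is that CTCAE has no grading for the event. It supplies a substitute scale; it does not say which events are to be graded. That is set by the sentence before it.

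**Step 3. Follow a non-serious drug effect, for example reduced libido reported at month 2.**

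- It meets the definition (5.1).
- It is recorded (5.3).
- Its relationship to study medication is assessed (5.4).
- It is checked against the seriousness criteria (5.2) and, in the usual case, is not serious.
- It is not directly related to phlebotomy or biopsy, so the grading sentence does not reach it.

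The event can be counted by arm, with its attributed cause and its seriousness. A grade is the one attribute that the text does not ask for.

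**Step 4. Are the endpoints touched?** The primary endpoint in Section 6.1 is the operating characteristics of PSA velocity for biopsy outcome. The secondary endpoints are PSA velocity in cases and controls and the operating characteristics of the other markers. None uses a severity grade.

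**Step 5. The status of biopsy.** Section 5.1 gives biopsy as an example of a research specific procedure. The list following Section 3.3 places it among procedures done as routine care regardless of the study, and Section 4.1 bills it to insurance on that basis. This labelling conflict is separate and adds no weight to the main point.

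**The case against.** The best defence is that the text is ambiguous and does not exclude drug events. The word *only* does not appear, and the fallback sentence refers to an adverse event generally, in a section that has just defined the term to include events under study medication. A site might well grade everything. That reading is possible, but nothing in the protocol states it. If it is what the sponsor meant, the parenthesis naming two procedures is misleading and still needs correcting.

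A second defence is that safety is largely covered and is not an aim of the trial. This stands. Drug events are recorded, attributed and classified for seriousness, and the gravest are caught by the serious adverse event criteria whatever their grade. Every stated endpoint is about markers. Section 6.2.1 justifies the placebo arm by its role in isolating the drug's effect on PSA change, and Section 4.2 cites experience from a trial of almost 19,000 men. With 90 placebo men planned for analysis, a comparison of grades between arms would be imprecise.

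A reader might go further and infer that drug effects will go ungraded in all 500 men and that severity by arm could not be tabulated. The documents do not support this. The case report form is not shown and may hold a severity field for every event. Only men who have an event have anything to grade, and under 4:1 allocation 500 × 4/5 = 400 men would receive finasteride. Nor is the lack of a stated summary by arm a fault, since that is commonly left to an analysis plan.

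**Conclusion.** The point holds as a mismatch of scope within Section 5 of the protocol. As written, the severity rule is narrower than the definition, recording and causality rules, and it requires no grade for non-serious adverse events of the study drug, including those the protocol itself lists. The size is modest: incidence, attributed cause and seriousness remain available, and no primary or secondary endpoint changes. The loss would be confined to the severity of non-serious drug effects.

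The conclusion rests on reading the grading sentence by its named scope and on the absence of any other severity rule in the protocol. If the case report form already asks for a grade on every event, the practical loss disappears and only the wording needs repair. The correction is worth making because the cost is small and ungraded events may not be recoverable afterwards.

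**What to change.** Reword the grading sentence in Section 5.1 so that all adverse events, including those related to study medication, are graded under the CTCAE version already named, keeping the existing 1-to-5 fallback where CTCAE has no term. Whether an event receives a grade would then no longer depend on the cause assigned to it. Confirm that the adverse event case report form carries a grade for every event.

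The cost is one sentence, possibly one form field, and a little more data entry at the month 1, 2 and 3 visits, where adverse events are already recorded. No visit, procedure or endpoint changes.

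As a minor separate correction, reconcile Section 5.1 with the routine-care list after Section 3.3 on whether the biopsy is a research specific procedure or routine care.

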**5.2 Serious Adverse Events**

A serious adverse event (SAE) is any untoward medical occurrence that:

1. Is fatal or life-threatening

2. Requires hospitalization or prolongation of existing hospitalization

3. Results in disability/incapacity

4. Is medically significant in that it may jeopardize the patient and may require medical or surgical intervention to prevent one of the outcomes listed above.

**5.3 Collecting** **and Recording Adverse Events**

Any AE or SAE occurring during the study must be documented in the subject’s medical record in accordance with the investigator’s normal clinical practice and on the AE or SAE case report form (CRF) for the study. An adverse event that occurs after study consent is signed but before research-related procedures will be recorded as medical history.

**5.4 Assessment of Causality**

The investigator is obligated to assess the relationship between any study-related procedure or study medication and the occurrence of each AE/SAE. The investigator will use clinical judgment to determine the relationship. Alternative causes, such as natural history of the underlying diseases, concomitant therapy, other risk factors, and the temporal relationship of the event to any study-related procedure or study medication will be considered and investigated.

Even in situations when an SAE has occurred and the investigator has incomplete information to include in the initial SAE report, the investigator will make an assessment of causality for every event prior to reporting it. The investigator may change his opinion of causality in light of follow-up information and amend the SAE case report form and report accordingly.

Adverse events will be reported annually to the IRB. SAEs meeting the IRB definition of Unanticipated Problems Involving Risk to Subjects or Others (UPIRSO) will be reported to the IRB within 7 days and within 48 hours if life-threatening or fatal. As Merck & Co will be providing finasteride and placebo, SAEs will also be reported to Merck within the same period. In addition, copies of all serious adverse experiences, which are possibly, probably, or definitely related to use of a Merck Product should be sent to Merck (Attn: Worldwide Product Safety; [contact]) within two working days. Additionally, any report of pregnancy occurring in association with use of a Merck Product should be sent to Merck (Attn: Worldwide Product Safety; [contact]).

**6. Data Analysis**

**6.1 Statistical Considerations for the Study**

Statistical endpoints of the study and definitions of terms are first provided for reference for the statistical plan for Specific Aims 2-5. Lists of analysis plans and power calculations follow for the required sample size of 500 (144 expected cancer cases in finasteride arm; 216 expected controls in finasteride arm; 90 subjects in placebo arm; 10% inflation for drop-out).

**Primary endpoint**:

- Operating characteristics (AUC, sensitivity and specificity) of 3-month finasteride PSA velocity for biopsy outcome.

**Secondary endpoints**:

- 3-month finasteride PSA velocity in cases and controls.
- Operating characteristics of initial and 3-month finasteride PSA, DRE, PCA3, and TMPRSS2:ERG (TMPRSS2:ERG) for biopsy outcome.

Definitions:

- Intermediate risk: risk of prostate cancer between 20% and 60% using PCPT Risk Calculator.
- 3-month finasteride PSA velocity: monthly change in log PSA while on finasteride. Clinical PSA baseline value (obtained within 3 months period prior to enrollment) and Research PSA Baseline (first) value is immediately prior to finasteride.
- Baseline (initial) PSA (DRE, PCA3, and TMPRSS2:ERG): PSA (DRE, PCA3, and TMPRSS2:ERG) value immediately prior to randomization.
- 3-month finasteride PSA (DRE, PCA3, and TMPRSS2:ERG): PSA (DRE, PCA3, and TMPRSS2:ERG) value at 3 months after 3-month of finasteride.
- 3-month placebo PSA (DRE, PCA3, and TMPRSS2:ERG): PSA (DRE, PCA3, and TMPRSS2:ERG) value at 3 months after 3-month of placebo.
- Sensitivity: The proportion of cancer cases with marker value exceeding a cutoff (specific to the choice of cutoff selected).
- Specificity: The proportion of control cases with marker value at or below a cutoff (specific to the choice of cutoff selected). Equals 100%-False Positive Rate.
- ROC curve: A graph of 1-Specificity (i.e. False Positive Rate) on the x-axis by Sensitivity on the y-axis. The closer the curve comes to the 45-degree diagonal of the ROC space, the less accurate the test.
- AUC curve: Area underneath the ROC curve ranging from 0 to 1, higher AUC indicates a better marker. Because a completely random guessing produces the diagonal line between (0, 0) and (1, 1), which has an AUC of 0.5, no realistic classifier should have an AUC less than 0.5.

*Possible Pitfalls and Alternative Strategies*:

As noted below in our statistical section, the statistical power of this study will rely on having a minimum of 144 events (prostate cancer cases) in finasteride arm to evaluate the 3-month finasteride ‘challenge’ test as an adjunct to prostate cancer detection. We expect a positive biopsy rate of 40% in men with intermediate risk of prostate cancer but will increase accrual as needed to reach this minimum number of events. We anticipate that some men may ‘drop out’ of the study’s participation due to perceived problems with the medication (e.g., perceived sexual dysfunction[56]) or if they simply change their mind related to the prostate biopsy. We plan on regular follow-up with all participants to keep them abreast of the study’s progress as well as new developments in prostate cancer detection. We have found that these regular follow-up telephone calls help maintaining subject interest in the trial. We have made conservative expectations on subject recruitment from our large Urology practice for accrual and do not anticipate problems reaching this number of events within the time of the study.

**6.2. Specific Aim 2**: To evaluate serum PSA velocity after a 3-month finasteride 'challenge' as a biomarker for prostate cancer on biopsy.

*Rationale: This aim is first needed to confirm that under finasteride, PSA indeed dropped more for non-cases than for subsequent cancer* cases (PSA velocity differed between cases and non-cases) *and that on its own has good (comparable to PSA alone) operating characteristics (sensitivity, specificity, and AUC).*

